### Outcome measurements

#### Primary outcome

The primary outcome is the change in the total score of the Spleen Qi Deficiency Symptoms Grading and Quantifying scale (SQD scale). The SQD scale is a modified version of the classic scale for assessing the degree of SQD in the Clinical Guideline of New Drugs for Traditional Chinese Medicine [21]. The SQD scale consists of 17 items regarding symptoms of SQD: (1) stomach distension, (2) abdominal distension, (3) physical fatigue and weakness, (4) mental fatigue and taciturnity, (5) loss of appetite, (6) abnormal stools, (7) stomach pain, (8) stomach tightness, (9) abdominal pain, (10) acid reflux, (11) belching, (12) nausea and vomiting, (13) abnormal bowel sounds, (14) powerless defecation, (15) sallow complexion, (16) loss of taste and hypodipsia, and (17) facial and limb edema. Items 1–6 are the main symptoms; the other items are secondary symptoms. The items are assessed for duration (0–3 points, only available for items 1–2 and 7–9), severity (0–3 points, not available for item 13), frequency per day (0–4 points; 0–3 points for item 5), and frequency per week (0–5 points). The total score is the sum of the scores of each item (the main symptoms are scored twice) and ranges from 0 to 292. A higher score indicates a more severe symptom. Compared with the classic scale, we added four items (items 1, 7, 10, and 11), defined the main symptoms according to TCM theory, and assessed each item for duration, severity, and frequency per day and per week rather than only for severity. The details of the SQD scale are presented in Additional file 1.

#### Secondary outcomes

The secondary outcomes are:Quality of life, assessed by a change in the Short Form 36 scale score [22]Performance status, assessed by a change in the ECOG questionnaire score [23]Changes from baseline in body weight and body mass indexProgression-free survival, assessed by pathological examination, computed tomography, and/or magnetic resonance imaging.

#### Safety outcomes

The safety outcomes are as follows:Adverse events (AEs), such as abnormal results (greater or less than 2 × normal reference interval) in routine blood, urine, and stool tests; liver function tests (alanine transaminase, aspartate aminotransferase, total bilirubin, direct bilirubin, and indirect bilirubin); kidney function tests (serum creatinine and urea nitrogen); coagulation function (prothrombin time, activated partial thromboplastin time, thrombin time, and fibrinogen); or electrocardiograms; as well as any other new-onset symptoms or diseases related or unrelated to the interventionSevere AEs (SAEs) are those AEs that lead to new or prolonged hospitalization, disability, admission to the intensive care unit, mortal danger, or death. SAEs will be reported to the principal investigator, the ethics committee of the hospital, and the Jiangxi Food and Drug Administration within 24 hWithdrawal due to AEs.

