### Patient eligibility

An eligible patient should meet all of the following criteria:Age between 18 and 70 yearsPathological diagnosis of gastric cancerUnderwent radical gastrectomy, radiotherapy, chemotherapy, and treatment of surgical complications (such as leaks, strictures, and marginal ulcers) 2 weeks to 1 year previouslyFair performance status indicated by a score on the Eastern Cooperative Oncology Group (ECOG) questionnaire ≤1.Signed the informed consent formDiagnosed with SQD syndrome based on TCM theory as follows:Primary symptoms of spleen deficiency: (1) poor appetite, (2) stomach or abdominal distention, and (3) abnormal stools (loose stools or diarrhea)Primary symptoms of qi deficiency: (1) physical fatigue and weakness and (2) mental fatigue and taciturnitySecondary symptoms: (1) loss of taste or hypodipsia, (2) stomach or abdominal pain, (3) stomach tightness, (4) nausea or vomiting, (5) abnormal bowel sounds, (6) leanness or puffiness, (7) sallow complexion, (8) powerless defecation, and (9) facial or limb edemaAuxiliary symptoms: pale, swollen, or scalloped tongue with a thin and white coating.Patients who meet two primary symptoms of spleen deficiency plus two primary symptoms of qi deficiency, two primary symptoms of spleen deficiency plus one primary symptom of qi deficiency plus one auxiliary symptom, or one primary symptom of spleen deficiency plus one primary symptom of qi deficiency plus two secondary symptoms plus one auxiliary symptom will be diagnosed with SQD syndrome.

An eligible patient should not meet any of the following exclusion criteria:Stage IV gastric cancer according to the Japanese classification criteria [20]Completed radical gastrectomy, radiotherapy, and chemotherapy more than 1 year previouslyImpaired liver function (total bilirubin > 2 × upper limit of normal (ULN), alanine transaminase > 2 × ULN, or aspartate aminotransferase > 2 × ULN), kidney function (serum creatinine > 2 × ULN), or hematopoiesis (neutrophil count < 0.5 × 10^9^/L, thrombocyte count < 20 × 10^9^/L, or absolute reticulocyte count < 15 × 10^9^/L)Obviously abnormal electrocardiogramSevere mental disorderOther severe diseases (e.g., multiple organ failure or acquired immune deficiency syndrome)Pregnant or breastfeedingAllergy to the test sampleUnwilling to provide personal information.

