### Study visits and outcome assessments

The duration of follow-up will be 2 years. Patients will visit at baseline and at 2, 4, 8, 26, 52, 78, and 104 weeks. At each visit, questionnaires and physical examinations will be completed, self-reported AEs will be recorded, and compliance will be assessed. At 8, 26, 52, 78, and 104 weeks, laboratory examinations and electrocardiograms will be performed, and cancer progression will be assessed. A detailed schedule of the trial is presented in Fig. 2.

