## Statistical analysis

Data analysis will be performed with Stata v14.0 (StataCorp LLC, College Station, TX, USA). The main primary outcome analysis will be based on the intention-to-treat data set, where the missing values will not be imputed and the patients who took unscheduled medications will be kept in their original group. We will also perform four sets of sensitivity analyses to test the robustness of the results of the main analyses, including (1) using the per protocol data set; (2) imputing missing data using various methods dependent on the proportion and distribution of the missing data; (3) excluding patients who become aware of the grouping accidentally during the trial, which also aims to estimate the placebo effects; and (4) excluding patients who took unscheduled medications. The analysis of secondary outcomes will be based on the per protocol data set, and the analysis of safety outcomes will be based on the safety data set only, both with no imputation. Interim data analyses will be performed after weeks 8 and 52.

Descriptive analysis will be conducted to explore the means and standard deviations of the continuous variables. We will assess the treatment effects by comparing the mean between-group differences of the continuous endpoints with a normal distribution using the independent *t* test. The skewed continuous variables will be described using medians and interquartile ranges. We will use the Mann-Whitney *U* test to assess the equivalency of the skewed continuous variable distributions. Moreover, we will describe categorical variables through their frequencies and percentages. We will evaluate the between-group differences using Pearson’s chi-square test for the cases with expected counts greater than 5 in more than 20% of cells and greater than 1 in any cell or Fisher’s exact test otherwise. We will perform subgroup analyses stratified by gastric cancer stage and chemoradiotherapy regimen for the primary outcome. We set α = 0.05 as the nominal type I error rate, which will be adjusted for the multiple *t* test using the O’Brien-Fleming group sequential method [25].

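### The laboratory adverse-event rule has no usable low-side limit and no baseline term, so low blood counts and low fibrinogen cannot be counted consistently

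*Protocol article*

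**What the plan says.** The Safety outcomes section gives one numerical rule for laboratory adverse events: "abnormal results (greater or less than 2 × normal reference interval) in routine blood, urine, and stool tests". The same list continues with liver and kidney tests, "coagulation function (prothrombin time, activated partial thromboplastin time, thrombin time, and fibrinogen", and electrocardiograms. It opens as a list of examples and closes with a catch-all for other newly arising symptoms or illnesses, whether or not they are related to the intervention.

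The Patient eligibility section writes its limits differently. For liver tests it names the upper limit ("alanine transaminase > 2 × ULN, or aspartate aminotransferase > 2 × ULN"). For blood counts it gives separate low cut-offs ("neutrophil count < 0.5 × 10^9^/L, thrombocyte count < 20 × 10^9^/L").

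On timing, Study visits and outcome assessments states: "At 8, 26, 52, 78, and 104 weeks, laboratory examinations and electrocardiograms will be performed". On analysis, the Statistical analysis section states: "the analysis of safety outcomes will be based on the safety data set only, both with no imputation". The article gives no low-side limit, grading scale or comparison with baseline for laboratory results.

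**The concern.** An interval has two ends, and multiplying it by 2 does not produce one lower bound. On the high side, the eligibility criteria suggest the intended meaning. On the low side nothing does, and the candidate readings give very different cut-offs. Blood counts and fibrinogen are tests where low results matter for safety. Patients may also enter as early as two weeks after radiotherapy or chemotherapy, so low counts at entry are foreseeable.

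The clause also makes no reference to the patient's own starting value. If a low count at entry already meets the rule, an unchanged result is recorded as an adverse event of treatment.

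What is at stake is the laboratory part of the adverse-event table by arm, in a trial that names safety as an aim. The same result could be counted at one hospital and not at another.

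**Working it through.** The plan states no figure that depends on this rule, so there is none to reproduce. The check is whether the phrase fixes a low-side cut-off.

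**Inputs from the article.** The rule itself ("greater or less than 2 × normal reference interval"), the entry limits, and five post-baseline laboratory visits (weeks 8, 26, 52, 78 and 104).

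**Inputs assumed.** The article gives no reference intervals. Three plausible intervals (L to U) were tried for each test:
- neutrophils: 1.8–6.3, 2.0–7.5 and 1.5–7.0 × 10^9/L
- platelets: 100–300, 125–350 and 150–400 × 10^9/L
- haemoglobin: 110–150, 120–160 and 130–175 g/L
- fibrinogen: 2–4, 1.8–3.5 and 2–4.5 g/L

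**Step 1: cut-off below which a result counts, by reading** (range over the three intervals)

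| Reading | Formula | Neutrophils | Platelets | Haemoglobin | Fibrinogen |
|---|---|---|---|---|---|
| A. Twice the lower limit | 2L | 3.0 to 4.0 | 200 to 300 | 220 to 260 | 3.6 to 4.0 |
| B. Twice the upper limit | 2U | 12.6 to 15.0 | 600 to 800 | 300 to 350 | 7.0 to 9.0 |
| C. One width below the lower limit | L − (U − L) | −4.0 to −2.7 | −100 | 70 to 85 | −0.5 to 0.1 |
| D. Interval doubled about its midpoint | (L + U)/2 − (U − L) | −1.25 to −0.45 | 0 to 25 | 90 to 107.5 | 0.75 to 1.0 |
| E. Half the lower limit | L/2 | 0.75 to 1.0 | 50 to 75 | 55 to 65 | 0.9 to 1.0 |

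**Step 2: do A and B make sense?** B flags every normal value. For A, suppose healthy values are normally distributed with 95% inside the interval. The mean is m = (L + U)/2, the SD is s = (U − L)/3.92, and the share flagged is Φ((2L − m)/s). For platelets 100–300, m = 200 and 2L = 200, so the share is Φ(0) = 50%. For neutrophils 1.8–6.3, m = 4.05 and s = 1.148, so the share is Φ((3.6 − 4.05)/1.148) = Φ(−0.39) = 34.8%. Over all the intervals, A flags about 19–35% of healthy neutrophil values, 50–65% of platelet values, essentially all haemoglobin values and 88–99% of fibrinogen values.

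**Step 3: do C and D make sense?** C can never be met for neutrophils or platelets, and is at or near zero for fibrinogen. D can never be met for neutrophils. For haemoglobin both give attainable cut-offs, but different ones.

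**Step 4: one result under all five readings.** Take platelets of 40 with interval 125–350. The cut-offs are A 250, B 700, C −100, D 12.5 and E 62.5, so the result is an adverse event under A, B and E but not under C or D. Take haemoglobin of 90 with interval 120–160. The cut-offs are A 240, B 320, C 80, D 100 and E 60, so it counts under A, B and D but not under C or E.

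**Step 5: baseline, low side.** A patient with neutrophils of 0.6 or platelets of 30 × 10^9/L is not excluded by the count limits, since 0.6 ≥ 0.5 and 30 ≥ 20. Both values lie below E for every assumed interval (0.6 < 0.75; 30 < 50). If nothing changes, the result meets the rule at all five visits. That is up to five records if events are counted by visit, or one patient with an event if counted by patient.

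**Step 6: baseline, high side.** The entry cap for ALT, AST, total bilirubin and creatinine is 2 × ULN, the same level as the high-side rule. No eligible patient starts above it, so the problem in Step 5 does not occur for these four tests.

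**The case against.** The strongest reply is that the phrase is loose rather than unworkable. A sensible investigator would read it as above twice the upper limit or below half the lower one, and a condensed article may leave limits for each test to the full protocol. The first part has force: half the lower limit is a usable rule. But it is not what the text says, and nothing in the article directs four hospitals to it. As for the second part, a missing detail would be no finding, but here a rule is stated and its low side fixes no cut-off.

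Several stronger readings are tempting, and the article does not support them.
- A reader might infer that low counts can never be adverse events. The list is one of examples and ends in a catch-all, so a new cytopenia can still be recorded. It would then rest on individual judgement, which is a problem of consistency, not total loss.
- A reader might infer that raised liver or kidney tests present at entry are counted as new. Step 6 rules this out for the four capped tests. A patient going from 1.95 to just above 2.00 × ULN (2.00/1.95 = 1.026, a 3% rise) is a new crossing, and any fixed cut-off has such cases.
- A reader might take the shares in Step 2 as expected false-positive rates. They rest on assumed intervals and on a reading that would call normal values abnormal. They show that the reading fails, not how often events will be miscounted.
- Applying the multiplier to electrocardiograms and qualitative urine or stool results is probably unintended. It is a matter of wording, not a separate defect.

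It is also fair that the effect is contained. Serious events are defined by their consequences, self-reported events are recorded separately at every visit, and the monitoring committee's safety criterion does not use this cut-off. Data collectors and assessors are blinded, so inconsistent classification should mostly add noise and not favour one arm.

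**Conclusion.** The point holds for the low side. The rule does not determine which low results are laboratory adverse events, and for neutrophils, platelets and fibrinogen the readings run from flagging normal values to flagging essentially nothing. The exact cut-offs depend on assumed reference intervals; the absence of a unique lower bound does not.

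The baseline gap is a second, narrower defect. It concerns low counts already present at entry, and it matters under readings such as half the lower limit. The closing words of the list may loosely imply that laboratory events must also be new, but the laboratory clause does not say so.

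The number of miscounted events cannot be estimated, because the article gives neither reference intervals nor the frequency of low counts at entry. The consequence is confined to laboratory adverse-event counts. The primary outcome and the sample size of 130 are untouched.

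**What to change.** Replace the phrase with separate high-side and low-side criteria, for example by adopting a named toxicity grading scale. Count a laboratory adverse event only when the result is new or worse than the patient's own baseline. Apply the numerical criterion only to tests that have a reference interval.

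The cost is wording in the protocol and analysis plan, plus a modest amount of reclassification. Stored results can be re-derived under the new rule without further tests, and the resulting counts may change. The rule should be fixed before unblinding. The comparison needs a baseline value for each test: the entry criteria imply one for the liver, kidney and blood-count limits, but for coagulation tests this should be confirmed against the schedule figure, which was not available here.

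### The adverse event definition names only new-onset symptoms, so worsening of the symptoms every patient has at entry may go unreported as an AE or SAE

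*Protocol article*

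**What the plan says.** **Safety outcomes.** The AE item opens with an illustrative list: "Adverse events (AEs), such as abnormal results (greater or less than 2 × normal reference interval) in routine blood, urine, and stool tests", then liver, kidney and coagulation tests and ECGs. It closes with "any other new-onset symptoms or diseases related or unrelated to the" intervention. That closing clause is the only wording on clinical symptoms. SAEs are defined as the AEs that have specified serious consequences, such as hospitalization or death. Withdrawal because of AEs is a separate safety outcome.

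**Patient eligibility.** SQD is an entry criterion, met by one of three routes:
- Route 1, which needs no tongue sign: "Patients who meet two primary symptoms of spleen deficiency plus two primary symptoms of qi deficiency"
- Route 2, with fewer qi symptoms but a tongue sign: "two primary symptoms of spleen deficiency plus one primary symptom of qi deficiency plus one auxiliary symptom"
- Route 3, which also draws on the secondary list: "one primary symptom of spleen deficiency plus one primary symptom of qi deficiency plus two secondary symptoms plus one auxiliary symptom"

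The auxiliary item is a tongue sign: "pale, swollen, or scalloped tongue with a thin and white coating".

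**Study visits and outcome assessments.** At each visit, "self-reported AEs will be recorded, and compliance will be assessed".

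**Compliance and withdrawal.** Sustained worsening of SQD symptoms is one of five reasons for withdrawal. None of the five is an AE.

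**Rules that use severe AEs.** Under Randomization and blinding, a severe AE leads to unblinding. Under Data collection and monitoring, an HGMX-related severe AE is one of the grounds on which the DMC may discontinue the trial.

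**The concern.** A definition tied to new onset does little harm when patients start without symptoms. Here symptoms are the condition of entry, and they are gastrointestinal and systemic: appetite, distension, stools and fatigue, with pain, nausea and edema among the secondary ones. These are also the complaints through which poor tolerance of a product eaten daily for 2 years could show itself. The same gap covers worsening of the comorbidities that the article expects, such as hypertension and diabetes.

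If a site follows the wording, a patient whose baseline diarrhoea becomes much worse has no AE. If that patient is admitted to hospital there is no SAE either, because an SAE must first be an AE. If the patient is withdrawn for deterioration, the article does not settle whether this counts as withdrawal because of an AE, and sites may classify it differently. The trial is meant to conclude on safety as well as efficacy, and its AE tables could be incomplete for these events.

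**Working it through.** **1. Symptoms at entry.** Inputs are the three routes under Patient eligibility, with the tongue sign not counted as a symptom.

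| Route | Spleen | Qi | Secondary | Minimum symptoms | Tongue sign needed |
|---|---|---|---|---|---|
| 1 | 2 | 2 | 0 | 2 + 2 = 4 | no |
| 2 | 2 | 1 | 0 | 2 + 1 = 3 | yes |
| 3 | 1 | 1 | 2 | 1 + 1 + 2 = 4 | yes |

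Enumerating every combination that satisfies at least one route confirms an overall minimum of 3. Every patient has at least one of appetite loss, distension or abnormal stools, and at least one of physical or mental fatigue. No single symptom is compulsory.

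**2. Where worsening of a baseline symptom can appear.**

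| Place | Is worsening named? | Is it safety data? |
|---|---|---|
| AE definition | no; the symptom clause requires new onset | yes |
| SAE definition | no; a subset of AEs | yes |
| Withdrawal because of AEs | no; depends on the AE definition | yes |
| Withdrawal reasons | yes, for SQD symptoms | not stated |
| SQD total score | yes, as a higher score | no, efficacy |

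The two places that register worsening are not designated as safety data, and the three safety outcomes do not name it.

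**3. Can the SQD score stand in for a safety count?** The Statistical analysis section compares arms by t test, or by medians and the Mann-Whitney U test if the data are skewed. It plans no count of patients who worsened. Missing values are not imputed in the main analysis, so a patient withdrawn for deterioration may contribute no later scores (assuming that visits stop at withdrawal, which the article does not say).

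**4. What an item-score table would need.** The Primary outcome section gives "severity (0–3 points, not available for item 13", so 17 − 1 = 16 items carry a severity grade. This reading reproduces the stated maximum of the scale:
- main items, scored twice: 2 × (2×15 + 3×12 + 11) = 2 × 77 = 154
- secondary items: 3×15 + 7×12 + 9 = 138
- total: 154 + 138 = 292, as stated

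There are 7 visits after baseline, so counting any one-grade rise on any item at any visit gives 16 × 7 = 112 chances per patient. If chance rises are independent with probability p per item and visit (an assumption), the share of patients flagged is 1 − (1 − p)^112:
- p = 1%: 68%
- p = 2%: 90%
- p = 5%: over 99%

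A table with so low a threshold would flag most patients in both arms and dilute a real difference.

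**5. Sample size.** With δ = 8.0, SD 14.5, two-sided α 0.05 and power 0.80, the result is 52 per arm; 52 / 0.80 = 65, total 130 as stated. This point does not affect it.

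**The case against.** The strongest reply is that the text does not exclude worsening. The AE list is introduced as examples, self-reported AEs are recorded at every visit with no stated onset filter, and an investigator may well record aggravated diarrhoea. The article also condenses a full protocol (version 3.2), and a standard operating procedure manual is planned. Neither is shown, and AE recording rules often sit there.

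Much of this stands. A reader might infer that worsening is never counted; the documents do not support that. A reader might also infer that no diarrhoea, nausea or pain can be an AE in this population. That is wrong too: a symptom that a patient lacked at baseline is new-onset when it appears. The gap concerns only what each patient already has.

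What does not stand is that this is merely detail left out. The article states a rule for symptoms and attaches a qualifier to it. The clause is also the residual one, meant to catch everything not already listed, and it catches only new onset. Introducing the list as examples does not tell a site to record worsening.

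A reader might further infer that the safety comparison is biased in favour of HGMX. The documents do not show this. The same definition applies to both blinded arms, and if HGMX relieves symptoms, the omitted events could fall mainly on placebo.

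**Conclusion.** The point holds as a badly fixed definition. Worsening of a symptom or disease present at baseline is not named as an AE, and SAEs and withdrawals because of AEs inherit the gap. It reaches all 130 planned patients, each with at least three entry symptoms, but only for the symptoms or diseases that the patient already has. Safety reporting may miss harm. Neither the number of missed events nor the direction between arms can be derived, because the article gives no rate of worsening.

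The conclusion assumes that sites apply the clause as worded and that no unseen document widens it. If the full protocol already counts worsening, only the article's wording and the link to the withdrawal reasons need correcting. The sample size and the primary analysis are unaffected.

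**What to change.** 1. In the AE definition, add that an AE includes any worsening from baseline, in severity or frequency, of a symptom or disease already present. The SAE definition then follows.
2. Reconcile the safety outcomes with the withdrawal reasons, so that it is clear whether a withdrawal for SQD deterioration counts as a withdrawal because of an AE. Check the amended definition against the unblinding rule and the DMC criterion, since both use severe AEs. What those rules should be is for the sponsor to decide.
3. In the safety set, report by arm the number of patients with a worsening AE and the number withdrawn for SQD deterioration. If item scores are tabulated as well, pre-specify a threshold that ordinary fluctuation does not meet; item 13 has no severity grade and needs its frequency scores.

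**Cost.** The change needs one sentence in the definition, a consistency check of three other passages and one extra table. AE counts will rise somewhat in both arms, because natural fluctuation is also recorded. The table needs no new data, provided that the questionnaires completed at each visit include the SQD scale. At submission 80 of 130 patients (62%) were already enrolled, so their earlier events were collected under the existing wording; item scores can recover these only in part, and the report should say so.
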